Activity and physical activity participation goals will be evaluated by the Goal Attainment Scaling–GAS [43, 44]. GAS is patient centred and has been widely used to quantify the achievement or fulfillment of goals previously defined in an intervention program [43–46]. In this study, goals will be selected by caregivers. In order to increase responsiveness, validity and reliability, three goals that can be affected by the treatment will be identified [47]. The first refers to performance of a sport-related motor activity, the second and third refers to attendance and involvement in leisure-time physical activities during sports or physical recreation participation (see example in Table 1). All GAS’ will be shared among caregivers and interventionists at baseline by another non-blinded assessor.

**Table 1 pone.0291488.t001:** Goal attainment scale examples.

Score	Meaning	Sports-related activity example	Attendance of physical activity participation	Involvement of physical activity participation
		*Parent’s goal*: *To dribble a soccer ball with control along the soccer field*	*Parent’s goal*: *To participate in soccer classes at least twice in a week*	*Parent’s goal*: *To be engaged at least 30 minutes when participates in school’s sports activities of one-hour duration*
**-2**	Current level	Dribbles a soccer ball during 4 meters of the soccer field without lose control of the ball	Does not participate in soccer classes in a week	Is not engaged at all during school’s sports activities
**-1**	Less than expected	Dribbles a soccer ball during 6 meters of the soccer field without lose control of the ball	Participate in soccer classes one day in a week	Is engaged in 15 minutes during school’s sports activities
**0**	Expected to achieve	Dribbles a soccer ball during 10 meters of the soccer field without lose control of the ball	Participate in soccer classes two days in a week	Is engaged in 30 minutes during school’s sports activities
**+1**	More than expected	Dribbles a soccer ball during 12 meters of the soccer field without lose control of the ball	Participate in soccer classes three days in a week	Is engaged in 45 minutes during school’s sports activities
**+2**	Much more than expected	Dribbles a soccer ball during 14 meters of the soccer field without lose control of the ball	Participate in soccer classes four days in a week	Is engaged in 60 minutes during school’s sports activities

*Activity Competence and sense of self*

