*Overall Participation at home, school and community*
**Participation and Environment Measure for Children and Youth—PEM-CY:** Will be used to assess participation at home, school and community [62, 63]. The measure identifies attendance and involvement of children in activities carried out at home, at school and in the community, as well as the characteristics of these environments that influence participation in six parts: frequency of participation, involvement of participation, desire to change participation, support for the environment, support for the environment and environmental resources [64, 65]. The PEM-CY has moderate to good internal consistency and test-retest reliability indices [62] and was translated and culturally adapted for the Brazilian population [58]. The PEM-CY it has been used as an outcome measure to assess the effects of participation interventions on individuals with ASD [66, 67].

*Randomization and blinding*. Children (n = 38) will be randomized into 2 groups (Sports Stars Brazil intervention and control group). Randomization will occur when 8 to 10 the child has been recruited and the allocation ratio will be 1:1. The randomization will be performed using a computer-generated random sequence to ensure equal allocation to each group. This sequence will be used to randomize children into the immediate group, or the control group. A new sequence will be used for each subgroup randomization until 36 children are allocated, or no further participants can be recruited. All assessments will be performed before the allocation of each subgroup. Thus, the use of the block randomization method is unlikely to increase the probability of identifying the allocation of participants.

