### Statistical methods

#### Sample size rationale

This study is designed to investigate the feasibility of conducting a future RCT to evaluate the effectiveness of Sports Stars and to build decision-making processes to guide the execution of a larger study, particularly concerning satisfaction, adherence. Despite of no sample size calculation is necessary in a feasibility trial, 15–20 subjects by group are suggested to determine if enrollment is sufficient to progress to a full RCT [33]. Our aim is to identify 36 potential participants to reach our target sample (18 per group) [70].

*Data analysis*. For process feasibility, participant recruitment and demographic/clinical data will be reported as means and standard deviations for continuous parametric data, medians and ranges for continuous non-parametric data, and frequencies and percentages for categorical data as per CONSORT recommendations [35]. Success criteria for feasibility will be reported descriptive and narratively, with accompanying 95% Confidence Interval (CI), when appropriate.

For scientific feasibility, as the objective of the study is to inform a definitive RCT, the analysis will focus on estimating treatment effect size and variance. No statistical significance tests (p value) or hypotheses regarding the effectiveness of the treatment will be performed. Treatment effects for secondary outcome measures will be presented as means, SD and CIs [35]. Considering a normal data distribution, effects sizes for each scientific feasibility outcome will be collected pre-intervention, immediately post intervention and at 12 weeks post intervention, using the following equation:

$$Cohen\overset{ˊ}{s}\;D=\frac{Mean\;pre-post\;change\;(treatment)-Mean\;pre-post\;change\;(control)}{\;Standard\;deviation\;(pooled)}$$

The following thresholds will be considered for interpretation of effect size: small (0.20 0.49), medium (0.50–0.79) and large (>0.80). High scores indicate better outcomes and positive effect sizes suggest benefit from Sports Stars over the control group [71]. The 95% CI will also be reported.

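### The one specified effect formula is an unadjusted change-score d with an unnamed pooled SD: unbiased, but less precise than ANCOVA and open to several readings

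*Protocol article*

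**What the plan says.** Under Statistical methods, Data analysis, the article states that "the analysis will focus on estimating treatment effect size and variance", so as to inform a definitive trial, and that no significance tests will be done. It then says that "effects sizes for each scientific feasibility outcome will be collected pre-intervention, immediately post intervention and at 12 weeks post intervention, using the following equation". The numerator is mean pre-post change in the treatment arm minus mean pre-post change in the control arm. The denominator is labelled only as a pooled standard deviation. The result is read against fixed labels: small 0.20 to 0.49, medium 0.50 to 0.79, large above 0.80. The same section adds that "Treatment effects for secondary outcome measures will be presented as means, SD and CIs" and promises a 95% CI for the effect size.

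Two other places bear on this. Under Randomization and blinding, children are allocated 1:1 in successive recruitment subgroups of 8 to 10: "A new sequence will be used for each subgroup randomization". In the GAS section, "three goals that can be affected by the treatment will be identified" for each child, and Table 1 gives the score -2 the general meaning "Current level".

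**The concern.** Estimating effect size and variance is the stated scientific purpose of the study, and the printed formula is how the effect size is to be obtained for every outcome. Two features of it matter.

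First, a change score uses the baseline with its slope fixed at 1. When the true slope is below 1, it over-corrects any chance baseline difference and leaves avoidable noise in the estimate. The subgroup, which restricts the randomisation, does not enter at all.

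Second, the pooled SD could be that of baseline, follow-up or change scores. These can give different values of d from identical data, all read against the same labels. A later planner who takes d from the report cannot tell which scale it is on. For GAS one of these readings cannot be computed.

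**Working it through.** **Inputs.** 36 children, 18 per arm (Sample size rationale); 1:1 allocation in subgroups of 8 to 10, so 36/10 = 3.6 to 36/8 = 4.5, or about four to five subgroups; the labels quoted above. The article gives no SD, no expected effect and no pre-post correlation r, so every r below is an assumption. Equal SDs at baseline and follow-up are also assumed. There is no effect-size or power figure in the plan to reproduce.

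**1. Precision.** In units of the outcome variance, the change score has variance 2(1 - r) and the baseline-adjusted score 1 - r². The ratio is (1 - r²) / [2(1 - r)] = (1 + r)/2, and interval width scales with its square root.

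| assumed r | variance ratio | width ratio | ANCOVA interval narrower by |
|---|---|---|---|
| 0.5 | 0.75 | 0.866 | 13% |
| 0.6 | 0.80 | 0.894 | 11% |
| 0.7 | 0.85 | 0.922 | 8% |
| 0.8 | 0.90 | 0.949 | 5% |

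These are large-sample values. One baseline slope and three contrasts among four subgroups cost four degrees of freedom: 36 - 2 = 34 becomes 30, and the t multiplier rises from 2.032 to 2.042. The covariates must also be estimated. A simulation with 36 children, four subgroups and no true subgroup effect gave average intervals narrower by about 12%, 9%, 6% and 3% for the four values of r.

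**2. Chance imbalance.** With 18 per arm, one standard error of the baseline difference is √(2/18) = 0.33 SD. The change-score estimate moves by (1 - r) times this: at r = 0.6, 0.4 × 0.33 = 0.13 SD. This averages to zero over randomisations.

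**3. Subgroups.** If subgroups explain a share s of the variance, an interval that ignores them is too wide by about 1/√(1 - s) - 1. For assumed s of 5%, 10% and 20%, this is 3%, 5% and 12%.

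**4. Choice of SD.** SD(change) / SD(baseline) = √(2(1 - r)), so d on the change SD is d on the baseline SD divided by that. Take a raw effect worth d = 0.50 on the baseline SD. The sample size read directly from d, at two-sided 0.05 and 80% power, is n per arm = 2(1.960 + 0.842)²/d², which is 63 for d = 0.50.

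| assumed r | multiplier | d on change SD | n per arm read from it |
|---|---|---|---|
| 0.3 | 0.85 | 0.42 | 88 |
| 0.5 | 1.00 | 0.50 | 63 |
| 0.7 | 1.29 | 0.65 | 38 |
| 0.8 | 1.58 | 0.79 | 26 |
| 0.9 | 2.24 | 1.12 | 13 |

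The label can change: 0.50 (medium) becomes 1.12 (large) at r = 0.9, and 0.55 (medium) becomes 0.55 × 1.58 = 0.87 (large) at r = 0.8. The test-retest coefficients in the outcome descriptions run from 0.84 to 0.99 for the Ignite Challenge, 10×5 Sprint Test, Muscle Power Sprint Test and physical literacy questionnaire. They are not correlations over 8 or 20 weeks, and some come from children with cerebral palsy, so they only make a high r plausible.

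**5. GAS.** If -2 is each child's current level, all 36 baselines equal -2 and the baseline SD is 0, so d on that SD has a zero denominator. Change is then follow-up plus 2, so the change SD equals the follow-up SD, d is defined on either, and baseline adjustment has nothing to remove.

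**The case against.** Several stronger readings are tempting, and the document does not support them.

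- *The formula discards baseline or is biased.* It does not discard baseline: each child's baseline is subtracted. Under 1:1 randomisation the difference in mean change is unbiased. The loss is one of precision, plus a shift conditional on chance imbalance.
- *It is the only effect summary planned.* It is the only between-group formula specified, but means, SDs and CIs are also promised, so part of the reporting asked for here may already be intended.
- *The GAS effect size is undefined.* Only if the baseline SD is meant. Nothing says so, and with a change score in the numerator the change SD is at least as natural a reading.
- *The smaller n in the last table is an error.* A d on the change SD gives the right n for a trial analysed by change scores. Harm arises only if it is carried into a trial analysed in another way.

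It can also be said that adjustment and the choice of standardiser belong in an analysis plan that is not shown. That holds for detail that the article leaves open, but the article prints a formula and applies it to every scientific outcome; a later plan would have to replace it, not merely add to it.

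The limits on consequence stand. The only success cut-offs are for response and completion, and none depends on d. At 18 per arm the approximate 95% CI around d = 0.50 is 0.50 ± 1.96 × √(2/18 + 0.25/72), or -0.16 to 1.16, so imprecision is large whichever estimator is used. Subgroup waves allocated 1:1 largely cancel between arms, so omitting them costs interval width, not validity. The precision gain and the SD discrepancy also pull apart: above r = 0.5 the first shrinks as the second grows.

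**Conclusion.** The point holds as a matter of precision and definition, not of bias. The specified change-score d gives up a variance factor of (1 + r)/2 against ANCOVA: intervals 13% to 5% narrower are available for assumed r of 0.5 to 0.8, a little less after the degrees of freedom are paid for, with a possible further gain from the subgroup term and no gain from baseline for GAS. The unnamed SD is the more consequential gap where r is high: no difference at r = 0.5, a factor of 1.58 at r = 0.8, and a zero denominator for GAS on the baseline reading. The sizes rest on assumed correlations and equal SDs over time, and the GAS point on -2 being every child's starting score, as Table 1 defines it. The change is worth making because effect size and variance are what this study is meant to hand to the next trial.

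**What to change.** In Data analysis, replace the formula as the main estimator. At 8 and at 20 weeks, estimate the arm difference by ANCOVA on the follow-up score, with baseline score and recruitment subgroup as covariates; for GAS, adjust for subgroup only. Report the raw adjusted difference with its 95% CI.

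Name the standardiser: the pooled baseline SD in general and the pooled follow-up SD for GAS, with a note that the GAS value is on a different scale and that the size labels are not directly comparable. For each outcome report the baseline, follow-up and change SDs and the pre-post correlation, so that a planner can convert between scales. Keep the change-score d as a supporting figure, with its SD stated.

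The cost is a change of wording and about four degrees of freedom for baseline and roughly four subgroups. No new data are needed beyond recording each child's subgroup.

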**Methods:**

This study will be conducted with 36 participants with ASD aged 6 to 12 years old following the CONSORT for pilot and feasibility recommendation. Participants will be randomly allocated into two groups. Intervention group will receive eight, weekly Sports Stars sessions. Each session will include of sports-focused gross motor activity training, confidence building, sports-education and teamwork development. Study assessments will occur at baseline, immediately post-intervention and 20-weeks post-randomization. First, we will assess process feasibility measures: recruitment, assessment completion, adherence, adverse events and satisfaction. Second, we will investigate the scientific feasibility of the intervention by estimating the effect size and variance at the level of achievement sports-related activity and physical activity participation goals (Goal Attainment Scaling), activity competence (Ignite Challenge, Test of Gross Motor Development-second edition, Physical Literacy Profile Questionnaire, Pediatric Disability Assessment Inventory–Computer Adaptive Test—PEDI-CAT—mobility, 10×5 Sprint Test and Muscle Power Sprint Test), sense of self (PEDI-CAT—responsibility), and overall participation at home, school and community, (Participation and Environment Measure for children and young people, PEM-CY).

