***Ignite Challenge*:** Measures accuracy and speed of locomotor and object control skills necessary for sports and active recreation activities [48]. It is a 13-item measure that can be used in children with ASD classified at ACSF levels I and II. The instrument total raw score is converted in percentage points. The higher the score, the better the performance. It can include “picture cards” for each test item to supplement evaluators’ demonstrations and improve understanding of each test item [49–51]. The *Ignite Challenge* has demonstrated excellent inter-rater (ICC = 0.91 (95% = 0.93, 0.99), intra-rater (ICC = 0.96, 95% = 0.90, 0.98) and rest-test (ICC = 0.91, 95% = 0.84, 0.95) reliability in Australian children with ASD (n = 47) [51].**Test of Gross Motor Development-2—TGMD-2:** Is used in children up three to 10 years, it assesses accuracy and quality of 12 fundamental motor skills, six of which are locomotor skills and six are object control skills. The total scores of each subtest are summed and represented as raw scores, which can be converted into motor quotients [52]. The TGMD-2 was validated and reliable for typical Brazilian children in the study by Valentini et al. [53] and has been used in children with ASD [54, 55]. Furthermore, it has been seen as a responsive measure in the Australian Sports Stars in children with CP [18]. Reliability of the TGMD-2 for children with ASD is currently being evaluated by our research group (ongoing study).**10×5 Sprint Test–(10×5ST) and Muscle Power Sprint Test (MPST):** The 10×5ST assesses agility [56, 57]. In the 10×5ST, participants need to run 5 m separated by 2 cones, 10 times continuously, making turns in the cones that mark the end of the five meters [57]. The 10×5ST has excellent inter-observer and test-retest reliability (ICC = 1.00 and 0.97) and good reported construction validity. An increase in agility of 3.2 seconds is considered a real change [54]. Participants muscle power will be evaluated by the Muscle Power Sprint Test–MPST [54]. The MPST measures muscle power by asking the participant to run as fast as possible for 15 m, 6 times, with a 10 second interval between each sprint. The MPST has high inter-observer and test-retest reliability (ICC = 0.97 and 0.99) for ambulant children with CP [56]. Reliability of the MPST and 10x5ST for children with ASD is currently being evaluated by our research group (ongoing study).**Pediatric Evaluation of Disability Inventory—Computer Adaptive—PEDI-CAT ASD:** Will be used to assess the domains of mobility (activity competence) and sense of self (responsibility) [58]. In the PEDI-CAT domain mobility the four-point scores are based on different levels of difficulty. The responsibility domain ranks items on a five-point scale, describing the division of responsibility between the caregiver and the child in managing complex, multi-step life tasks. The PEDI-CAT was adapted and presented reliability to be used by children with autism [59]. It was translated and culturally adapted for the Brazilian population aged 0–21 years [60].**Physical Literacy Profile Questionnaire–PLPQ:** Assesses the components of physical literacy (physical, cognitive, social and psychological) of children [61]. The questions are related to performance and satisfaction in the physical, social, psychological and cognitive competencies. Each item assesses performance on a scale of 0 to 2 and each item assesses the child/adolescent/young adult’s performance satisfaction on a scale of 1–10 points. The higher the score, the higher the level of performance and satisfaction. The QPAF is in the process of being validated by our research group, preliminary data showed good test-retest reliability for children with CP (ICC = 0.84; IC [95%]: 0.74–0.91) (data not published yet) [61].

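### The single direction rule for all effect sizes is wrong for the 10×5 Sprint Test, where a shorter time is the better result

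*Protocol article*

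**What the plan says.** The Data analysis text, under Statistical methods in the Protocol article, gives one formula: the mean pre-post change under treatment minus the mean pre-post change under control, divided by a pooled standard deviation. It applies to all the scientific outcomes: "effects sizes for each scientific feasibility outcome will be collected pre-intervention, immediately post intervention and at 12 weeks post intervention". The sign is then read by one rule with no exception: "High scores indicate better outcomes and positive effect sizes suggest benefit from Sports Stars over the control group".

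The Methods paragraph of the Abstract lists the outcomes that the formula covers. The 10×5 Sprint Test is among them, under activity competence: "10×5 Sprint Test and Muscle Power Sprint Test), sense of self (PEDI-CAT—responsibility".

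The Outcomes section describes that test as a run over a fixed course: "participants need to run 5 m separated by 2 cones, 10 times continuously". It gives the size of a meaningful change in seconds: "An increase in agility of 3.2 seconds is considered a real change". For the Ignite Challenge, another outcome in the same list, the same section says: "The higher the score, the better the performance".

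The article nowhere mentions reverse scoring, conversion to speed or a change of sign for the sprint test.

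**The concern.** A rule that reads every positive d as benefit works only if all outcomes point the same way, or are made to before d is computed. Here they do not. The Ignite Challenge improves upwards. A fixed-distance run measured in seconds improves downwards.

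The protocol is not silent on direction, so this is not a detail left to a later analysis plan. It states a rule, and the rule is wrong for a listed outcome. Because no significance tests are planned, the effect sizes and their confidence intervals are the main scientific output passed to the full trial. At stake is the reading of one of the nine outcomes announced in the Background: an improvement in agility could be taken as a result in favour of usual care. The wording of the 3.2 s criterion adds to the risk, since it attaches an increase to a number that must fall when agility improves.

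**Working it through.** The article gives no numerical effect size to reproduce. The check therefore applies its formula to a benefit of known direction.

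**Inputs**
- Benefit: Sports Stars children become 3.2 s faster and controls do not change. The 3.2 s is the article's own real-change value (Outcomes); no change in controls is an assumption.
- Group size: 18 per group (Sample size rationale), used only for an illustrative confidence interval.
- Pooled SD: not given. Assumed values are 2, 3.2, 4, 6 and 8 s.
- Order of subtraction: the term pre-post change does not fix it, so both orders are tried.
- Lower is better for the sprint test: the article does not say this in words. It follows from a fixed distance measured in seconds.

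**Formula**

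d = (mean change, treatment − mean change, control) / SD

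**Order A, change = post minus pre.** The sprint change is −3.2 s under treatment and 0 under control, so d = (−3.2 − 0)/SD. For comparison, the last column takes a higher-is-better scale with a benefit of the same standardised size.

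| Assumed SD (s) | d, 10×5 Sprint Test | d, higher-is-better scale |
|---|---|---|
| 2 | −1.60 | +1.60 |
| 3.2 | −1.00 | +1.00 |
| 4 | −0.80 | +0.80 |
| 6 | −0.53 | +0.53 |
| 8 | −0.40 | +0.40 |

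The rule reads the last column correctly. It reads every entry in the sprint column as favouring control, although the children improved.

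An approximate interval for SD 4 s, with n = 18 per group:
- SE = √(2/n + d²/(4n)) = √(2/18 + 0.64/72) = √0.120 = 0.346
- 95% CI = −0.80 ± 1.96 × 0.346 = −1.48 to −0.12

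In this example the whole interval lies on the side that the rule assigns to control.

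**Order B, change = pre minus post.** All signs flip. The sprint test now gives +1.60 to +0.40, as the rule wants, but a benefit on any higher-is-better scale gives −1.60 to −0.40. The error has moved to the Ignite Challenge and similar scales.

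**Result.** No single order of subtraction makes the rule true for all the listed outcomes.

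**With the sign reversed for the sprint test under order A:** d = −(−3.2 − 0)/SD = +1.60, +1.00, +0.80, +0.53 and +0.40. A positive d then means benefit on both kinds of scale. The SD and the width of the interval do not change.

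**The case against.** The strongest reply is that the harm is unlikely. The formula does not say which measurement is subtracted from which. The article describes a gain on this test as a gain in agility, which suggests that its authors know which way improvement runs. The sentence on direction may be a shortened convention that a sensible analyst would adapt. Means and SDs are to be reported as well, so a reader could see which group became faster. The two numerical success criteria are a response rate of at least 10% and completion by at least 80%, so no effect size decides whether the full trial goes ahead. The test might even be dropped: its reliability in children with ASD is still being studied, and the Discussion allows measures with unsatisfactory properties to be excluded.

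Most of this stands, and it limits the severity. It does not make the rule correct. The open order of subtraction only moves the error, and an analyst who corrected the sign would be departing from the published rule.

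A reader might also infer more than the article supports:
- **That the rule fails for the PEM-CY.** One of its listed parts concerns desire for change ("frequency of participation, involvement of participation, desire to change participation"), but the article gives no scoring direction for that part and plans no separate effect size for it.
- **That it fails for the Muscle Power Sprint Test.** The article describes this as a measure of muscle power and states no scoring unit. Nothing shows that sprint times would be analysed.
- **That blinding the statistician would hide the reversal.** Blinding to group does not conceal whether a shorter time is better.

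**Conclusion.** The point holds for the 10×5 Sprint Test. The statement that high scores are better is wrong for a time in seconds over a fixed course, and no order of subtraction makes the sign rule valid for both this test and the higher-is-better scales.

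A reader might infer that a benefit is bound to be published as favouring control. The article does not support that. The misreading follows if change is taken as post minus pre and the rule is applied literally; an analyst may notice and correct it.

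The error is one of sign only; |d|, the SD and the width of the interval are unaffected. The figures of 1.60 to 0.40 rest on assumed SDs of 2 to 8 s and on no change in controls. By the article's own thresholds they run from large to small, so no particular size should be attached to the problem. The existence of the sign error does not depend on the SD. One of nine outcomes is affected directly. Severity is moderate to minor: worth correcting before analysis, but no threat to the feasibility conclusions.

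**What to change.** In the Data analysis text:
1. Define change as post minus pre.
2. State the direction of benefit for each scientific feasibility outcome.
3. For the 10×5 Sprint Test, multiply the change by −1 before computing d. Do the same for any other score that is confirmed to be lower-is-better.
4. Replace the blanket statement that high scores are better with a statement that, after this alignment, a positive d favours Sports Stars on every outcome.

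In the Outcomes section, word the 3.2 s real change as a decrease in time.

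The cost is a few lines of text. Design, data collection and sample size do not change.
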